3. SCIENTIFIC JUSTIFICATION AND GENERAL DESCRIPTION

3.1. Current State of Knowledge

3.1.1. On the Pathology

Major abdominal surgeries can be performed via laparotomy when a minimally invasive (coelioscopic) approach is not possible. Laparotomy involves a large incision through the abdominal skin and musculature to access the internal organs, and it causes significant pain that delays the patient’s postoperative recovery. Managing pain in these patients is therefore a major concern for perioperative care providers. Pain control relies on two main techniques: epidural anesthesia and intravenous lidocaine.

3.1.2. On Reference Treatments/Strategies/Procedures and Those Under Study

Epidural anesthesia (EPA) is the gold standard for managing laparotomy pain. However, it induces sympathetic blockade and can cause hypotension, which may be dangerous for the patient and lead to intra- or postoperative organ dysfunction. Therefore, the infusion of local anesthetics through the epidural catheter is typically started only after the high-risk surgical stages are over – in practice, at the time of surgical closure. Intravenous lidocaine has multiple effects: anti-arrhythmic, anesthetic, analgesic, anti-inflammatory, antithrombotic, bronchodilatory, neuroprotective, and even antimicrobial properties. IV lidocaine infusion does not cause vasoplegia, whereas epidural anesthesia blocks sympathetic nerves and can reduce vascular resistance. The clinical analgesic efficacy of IV lidocaine has been confirmed by a 2018 meta-analysis. It is administered at the start of surgery (during induction) and continued intraoperatively until closure, at which point it is stopped. IV lidocaine via infusion pump is thus proposed as an alternative to epidural analgesia when the latter is contraindicated or if epidural placement fails. Depending on the chosen analgesic technique, there is a period not covered by local anesthetics: for lidocaine, this gap is at closure and immediate postoperative; for epidural, it is almost the entire intraoperative period until closure. This is why practitioners at our university hospital combine these two techniques. We know anecdotally from discussions with colleagues that this combined approach is also used in other hospitals, but no study has been conducted on the subject. However, there is a theoretical risk of local anesthetic toxicity with this combination, which dissuades some clinicians from using both techniques despite the potential significant benefit for patients. The combination of two local anesthetics is feasible only if we consider the kinetics of their plasma concentrations with each technique. Lidocaine is administered IV, whereas ropivacaine is administered into the epidural space. The systemic absorption of ropivacaine infused epidurally has been studied in several works, which showed plasma concentrations very far from toxic thresholds. This finding is reassuring for its concomitant use with IV lidocaine. However, we must consider whether there is any pharmacodynamic potentiation between these two drugs. Before attempting to demonstrate any clinical advantage of this combination for patient care, it is imperative to first ensure that combining them does not increase their toxicity. To date, although this combination is in widespread use, no study has been carried out to demonstrate its safety. Our study aims to show that toxic plasma thresholds are not reached when these two techniques are combined. We will also monitor for clinical signs of local anesthetic toxicity (central nervous system effects: seizures, dizziness, paresthesia, tongue numbness, hyperacusis, tinnitus, visual disturbances, dysarthria, muscle contractions, tremors; hypoesthesia; cardiac effects: bradycardia, tachycardia, conduction disturbance potentially progressing to cardiac arrest) when they are used together.

3.2. Research Hypotheses and Expected Results

Our hypothesis is that combining continuous IV lidocaine infusion with epidural anesthesia during management of a major abdominal surgery does not increase the plasma concentrations of local anesthetics beyond toxic thresholds. Through repeated blood sampling, we hope to show that plasma levels of the local anesthetics remain well below toxic values. Furthermore, by observing an absence of adverse events related to local anesthetic use (central nervous system effects – which are rare – such as seizures, dizziness, loss of consciousness, paresthesia, tongue numbness, hyperacusis, tinnitus, visual disturbances, dysarthria, muscle tremors; hypoesthesia; and cardiac effects such as bradycardia, tachycardia, conduction disturbances up to cardiac arrest), we hope to demonstrate no cumulative cardiac or neurological toxicity when both are used together.

3.3. Rationale for Methodological Choices

Lidocaine and ropivacaine are both metabolized in the liver. The toxic thresholds for these two local anesthetics are becoming well known: for lidocaine, the therapeutic plasma range is 1.4 to 5 µg/mL, and toxicity can begin at concentrations above 5 µg/mL. Neurotoxic effects appear around 15 µg/mL and cardiotoxicity around 21 µg/mL. For ropivacaine, the usual maximal total venous concentration not to exceed is about 2.2 µg/mL. The half-life of IV lidocaine is 80–110 minutes. Ropivacaine, when administered into the epidural space, is absorbed completely in a biphasic manner, with half-lives of approximately 14 minutes and 4 hours for the two phases in adults. Its slow absorption is the rate-limiting step in its elimination, leading to a longer apparent elimination half-life after epidural administration compared to IV administration. In our study, five plasma measurements of lidocaine and ropivacaine will be taken at different times during surgery and up to 24 hours post-op: lidocaine level at 30 minutes after the bolus, lidocaine level at the end of its infusion (i.e. at surgical closure), lidocaine level at 2 hours after starting the epidural, ropivacaine level at 2 hours after starting the epidural, and ropivacaine level at 24 hours after starting the epidural. Achieving a steady plasma level during a continuous infusion takes more than 60 minutes, which is why an initial bolus is recommended. Given the rapid distribution after a bolus, it’s recommended to start the maintenance continuous infusion promptly if a stable plasma concentration is to be maintained for infusions longer than 20 minutes. This justifies our first blood draw at 30 minutes after the lidocaine bolus. Thereafter, the plasma concentration remains stable around a level determined by the dose and infusion rate, which is why we will measure at the moment of stopping the infusion to capture the intraoperative plasma level of lidocaine. For the epidural, systemic absorption is gradual. Studies show a linear increase in plasma levels during the continuous infusion; the 2-hour ropivacaine level will provide an initial indication of ropivacaineemia. The lidocaine sample taken at the same 2-hour mark will indicate the residual lidocaine concentration at the time ropivacaine levels are rising, giving insight into the overlap period of both local anesthetics, and whether lidocaine’s decline follows the expected pattern when another local anesthetic is present. Finally, the ropivacaine level at 24 hours post-epidural induction will reflect the average plasma concentration after a full day of continuous epidural ropivacaine infusion. Lidocaine is not measured at 24h because it will have been fully eliminated by that time.

3.4. Benefit/Risk Assessment

Demonstrating the safety of this combination will firstly allow us to standardize our practices. It will then enable further research to demonstrate the superiority of combining these two techniques compared to epidural analgesia alone or IV lidocaine alone. In this way, we could improve recovery after these major surgeries that cause severe pain and morbidity. The local anesthetics will be used according to current recommendations and good practice guidelines, and their usage will not be altered by this research. The only additional risk induced by this study is related to the extra blood samples beyond the routine tests normally performed during patient care. Blood draws will be done through the arterial catheter (placed as usual for the surgery). This arterial line is in most cases kept for 24h (when patients are in a step-down or intensive care unit). If the arterial line is removed earlier, the 24h post-epidural ropivacaine sample will be taken by a nurse via venipuncture at the investigator’s request (or by the investigator).

3.5. Expected Outcomes

Demonstrating the safety of this combination will initially allow us to standardize our practices. Combining IV lidocaine analgesia with epidural anesthesia appears very promising for managing patients undergoing major abdominal surgery, as this combination can modulate pain via different pathways. Currently, no study has shown the superiority of this combination over other analgesic techniques. Proving that no additional adverse effects occur when these two techniques are combined will allow those comparative studies to be performed and help identify the best therapeutic strategy for patients. This could optimize patients’ postoperative recovery.

4. OBJECTIVES OF THE RESEARCH

4.1. Primary Objective

The primary objective of this study is to evaluate the plasma concentrations of lidocaine and ropivacaine when an epidural anesthesia is combined with intravenous lidocaine during a major abdominal surgery.

4.2. Secondary Objectives

The secondary objective is to identify any undesirable side effects related to local anesthetics in connection with the combination of epidural anesthesia and intravenous lidocaine during a major abdominal surgery. Specifically, we will look for signs of local anesthetic toxicity, including central nervous system symptoms (seizures, dizziness, loss of consciousness/“attacks,” paresthesia, tongue numbness, hyperacusis, tinnitus, visual disturbances, dysarthria, muscle contractions, tremors, hypoesthesia) and cardiac symptoms (bradycardia, tachycardia, conduction disturbances up to cardiac arrest) potentially attributable to this combination.

5. ENDPOINTS

5.1. Primary Endpoint

The primary endpoint is the plasma concentration of ropivacaine and lidocaine falling outside the safe range at the various time points of patient management. We will obtain five plasma measurements of lidocaine and ropivacaine at different times during surgery and up to 24 hours postoperatively: lidocaine level at 30 minutes after the bolus injection, lidocaine level at the end of its infusion (i.e. at surgical closure), lidocaine level at 2 hours after induction of the epidural, ropivacaine level at 2 hours after induction of the epidural, and ropivacaine level at 24 hours after induction of the epidural. The toxic thresholds of these two local anesthetics are known: for lidocaine, the safe plasma range is 1.4 to 6 µg/mL; neurotoxicity appears from 15 µg/mL and cardiotoxicity from 21 µg/mL. For ropivacaine, the usual maximum total venous concentration not to exceed is around 2.2 µg/mL. Any single measurement above the toxicity threshold will be considered an occurrence of toxicity.

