Contraindication to thoracic epidural placement (e.g. coagulation disorders, localized or systemic infection, shock or uncorrected hypovolemia, respiratory failure if block level > T7, severe aortic or mitral stenosis, obstructive cardiomyopathy, severe uncompensated heart failure)

Allergy to local anesthetics; Contraindication to IV lidocaine (acute porphyria, unpaced atrioventricular conduction disorders, severe heart failure, severe liver failure, uncontrolled epilepsy, treatment with Class I antiarrhythmics)

Contraindication to ropivacaine (allergy to local anesthetics, acute porphyria)

Major hepatectomy with vascular clamping

Patient refusal to participate

Minor (age < 18)

Patient under guardianship/curatorship or deprived of liberty

Pregnant, parturient, or breastfeeding women

Cognitive impairment precluding giving informed consent

STUDY TREATMENT/PROCEDURE: Induction with IV lidocaine 1.5 mg/kg followed by continuous infusion at 2 mg/kg/h (per SFAR guidelines), stopped at surgical closure. Immediately at discontinuation, initiation of thoracic epidural analgesia with ropivacaine, infused for 24h at a minimum of 5 mg/h after an initial minimum bolus of 5 mg via the epidural catheter. As part of the study, blood samples will be taken for lidocaine levels 30 minutes after the induction bolus, at the end of the continuous infusion, and 2 hours after starting the epidural ropivacaine infusion. Blood samples for ropivacaine levels will be taken 2 hours after starting the epidural and 24 hours after starting the epidural.

ENDPOINTS: The primary endpoint is the plasma concentration of ropivacaine and lidocaine falling outside the safe range at the various time points of management. For lidocaine, the safe plasma range is 1.4 to 6 µg/mL; neurotoxicity appears from 15 µg/mL and cardiotoxicity from 21 µg/mL. For ropivacaine, the usual maximum safe venous concentration is around 2.2 µg/mL. The secondary endpoint is the occurrence of clinical systemic toxicity of local anesthetics within 48 hours postoperatively, defined by any of the following events: central nervous system disturbances (seizures, dizziness, paresthesia, tongue numbness, hyperacusis, tinnitus, visual disturbances, dysarthria, muscle twitching, tremors, hypoesthesia) or cardiac disturbances (bradycardia, tachycardia, conduction disorder potentially progressing to cardiac arrest). This composite endpoint will be counted if at least one of the above events is present.

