12.2. Statistical Methods

Quantitative variables will be described as mean ± standard deviation and median [range]. Qualitative variables will be described as percentages with 95% confidence intervals

Primary endpoint analysis: We will calculate the percentage of patients who have at least one plasma concentration of ropivacaine or lidocaine outside the safe range. A 95% confidence interval (using an asymptotic or exact method as appropriate) will be computed for this percentage.

Secondary endpoint analysis: The percentage of patients experiencing a toxic event will be calculated with a 95% confidence interval (asymptotic or exact method). All statistical analysis will be performed using SAS software version 9.4

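### The lidocaine upper limit behind the primary event is 6 µg/mL in the endpoint and 5 µg/mL in the rationale, and section 5.1 closes with a one-sided, unnumbered threshold that conflicts with its own two-sided definition

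*Protocol*

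**What the plan says.** The protocol gives an upper limit for lidocaine in three places.

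- Section 5.1 (Primary Endpoint): "for lidocaine, the safe plasma range is 1.4 to 6 µg/mL; neurotoxicity appears from 15 µg/mL and cardiotoxicity from 21 µg/mL".
- Section 1 (Summary, endpoints): "For lidocaine, the safe plasma range is 1.4 to 6 µg/mL".
- Section 3.3 (Rationale for Methodological Choices): "for lidocaine, the therapeutic plasma range is 1.4 to 5 µg/mL, and toxicity can begin at concentrations above 5 µg/mL". The same paragraph then gives about 15 µg/mL for neurotoxicity and about 21 µg/mL for cardiotoxicity, as 5.1 does.

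It describes the event in two ways.

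- By range. Section 5.1 opens: "The primary endpoint is the plasma concentration of ropivacaine and lidocaine falling outside the safe range". Section 12.2 analyses "the percentage of patients who have at least one plasma concentration of ropivacaine or lidocaine outside the safe range". Section 12.1 sizes the study on the same idea.
- By threshold. Section 5.1 closes: "Any single measurement above the toxicity threshold will be considered an occurrence of toxicity". The hypothesis in section 3.2 is worded similarly: the combination "does not increase the plasma concentrations of local anesthetics beyond toxic thresholds".

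Neither 12.2 nor 3.2 repeats a number.

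**The concern.** The primary result is a single percentage from 50 patients, and a lidocaine cut-off is one of the rules that turn concentrations into events. If two sections disagree on that cut-off, two analysts working from the same protocol can code the same patient differently. The closing sentence of 5.1 adds a second uncertainty: it does not say which number it means, and it ignores the lower end of the range that the opening sentence includes.

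The study is single-arm and open-label, and it aims to show that toxic plasma levels are not reached. Its headline percentage should therefore rest on a rule that can be read in only one way before the concentrations are known.

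**Working it through.** **1. The plan's own figure.** Section 12.1 assumes 10% with N = 50 and states ±8%. The asymptotic half-width is 1.96 × √(0.10 × 0.90 / 50) = 0.083, or ±8.3%, which rounds to the stated figure. At 50% it is 1.96 × √(0.50 × 0.50 / 50) = 0.139, against the stated ±14%. At a given proportion this precision does not depend on the cut-off. What the cut-off changes is which patients count.

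**2. The limits side by side.**

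| Place | Label | Lower | Upper | Neurotoxicity | Cardiotoxicity |
|---|---|---|---|---|---|
| Summary | safe | 1.4 | 6 | 15 | 21 |
| 5.1 | safe | 1.4 | 6 | 15 | 21 |
| 3.3 | therapeutic | 1.4 | 5 | about 15 | about 21 |

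(all in µg/mL)

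Three of the four figures agree and only the upper limit differs. The label differs too, but 3.3 adds that toxicity can begin above 5, so the change of label does not reconcile the two. A level of 5.5 µg/mL is safe under 5.1 and possibly toxic under 3.3.

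**3. The event rules side by side.**

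| Lidocaine level (µg/mL) | Outside 1.4 to 6 (5.1 opening, 12.2) | Above the threshold, read as 6 (5.1 closing) | Above 5 (3.3) |
|---|---|---|---|
| below 1.4 | event | not an event | not above the limit |
| 1.4 to 5 | not an event | not an event | not above the limit |
| above 5, up to 6 | not an event | not an event | above the limit |
| above 6 | event | event | above the limit |

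The rules disagree in two rows. The third row is the conflict between 5 and 6. The first row is the conflict between a two-sided and a one-sided rule, and it remains even if the upper limit is settled.

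**4. Size of the conflict between 5 and 6.** One patient in 50 is 1/50 = 2 percentage points. This applies only to a patient who is not already an event by another route. The exact (Clopper-Pearson) 95% intervals for three such patients are:

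- 0/50: upper limit 1 − 0.025^(1/50) = 0.0711, giving 0 to 7.1%.
- 3/50 = 6%: lower limit is the 2.5% point of Beta(3, 48) = 0.0125; upper limit is the 97.5% point of Beta(4, 47) = 0.1655; giving 1.3 to 16.5%.

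The planning assumption of 10% corresponds to 0.10 × 50 = 5 patients. The number three is an illustration and does not come from the protocol.

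**5. How many patients might lie between 5 and 6?** The protocol gives no expected concentrations. Assume a single lognormal level, P(>c) = 1 − Φ[(ln c − ln median)/s] with s = √ln(1 + CV²):

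| Median (µg/mL) | CV | P(>5) | P(>6) | Difference |
|---|---|---|---|---|
| 2 | 30% | 0.1% | 0.01% | about 0.1 points |
| 3 | 30% | 4.1% | 0.9% | 3.2 points |
| 3 | 50% | 14.0% | 7.1% | 6.9 points |
| 4 | 30% | 22.4% | 8.4% | 14.0 points |
| 4 | 50% | 31.8% | 19.5% | 12.3 points |

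The effect runs from negligible to about 14 points, depending on assumptions that the protocol does not supply.

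**6. Does the lower end matter?** Section 3.3 gives a lidocaine half-life of 80 to 110 minutes. Assuming simple mono-exponential decline from the stop of the infusion, the fraction left after 120 minutes is 2^(−120/80) = 0.354 to 2^(−120/110) = 0.469. A 2-hour level below 1.4 µg/mL then follows from any stop-time level below 1.4/0.469 = 3.0 to 1.4/0.354 = 4.0 µg/mL. Under the literal two-sided rule such a patient is an event, and under the closing sentence of 5.1 not.

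**The case against.** The strongest reply is that the conflict lies between background and endpoint. Section 3.3 explains the sampling times and defines no event. Both places that state the endpoint agree on 6, and the sample size and analysis sections use the same safe-range wording. On this view the primary rule is already fixed and only the rationale needs tidying. Much of this stands: 6 is the most natural reading, and coding the event at another figure would depart from the written endpoint.

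A reader might go further and infer that 15 or 21 µg/mL could serve as the primary cut-off, so that almost no patient would be an event. The documents do not support that. Those figures are labelled as the onset of neurotoxicity and cardiotoxicity and are never called limits of the safe range, and using them would contradict 12.2.

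A reader might also infer that the endpoint depends wholly on the lidocaine upper limit. It does not: a ropivacaine level above about 2.2 µg/mL counts, and under the two-sided wording so does lidocaine below 1.4 µg/mL.

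Finally, the study is descriptive, without a hypothesis test, and 12.2 reports medians and ranges, so a maximum above 5 or 6 should be visible. That softens the consequence. It does not tell an analyst how to code a level of 5.5 or of 1.2 µg/mL for the headline percentage.

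**Conclusion.** The point holds as an internal contradiction in the definition of the primary event, in two parts. First, the lidocaine upper limit is 6 µg/mL in 5.1 and the summary and 5 µg/mL in 3.3, with no reason given for the difference. Second, the closing sentence of 5.1 is one-sided and unnumbered, against a two-sided range in its opening sentence and in 12.2.

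The first part is worth 2 percentage points per patient whose only out-of-range value lies between 5 and 6 µg/mL. How many such patients there will be is unknown. The intervals for 0/50 and 3/50 show scale and are no forecast. The second part could involve more patients, but that rests on the assumed mono-exponential decline and on stop-time levels that the protocol does not give.

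One might infer that the sponsor intends to choose the cut-off after seeing the data. Nothing in the protocol indicates that. The finding is only that the text permits more than one coding. A statistical analysis plan could select one, but it would still contradict a section of the protocol.

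**What to change.** Before any concentration is read:

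1. Reconcile the summary, 3.3 and 5.1 to one lidocaine upper limit, with its source. Which limit is right is for the investigators; this review takes no position.
2. In the closing sentence of 5.1, replace the unnumbered threshold with that number.
3. State in 5.1 whether a lidocaine level below 1.4 µg/mL is an event.
4. Repeat the same numeric definition in 12.2.

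Counts above the other quoted lidocaine figures can be tabulated as a descriptive supplement. This is optional.

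The cost is wording in four sections and, if wanted, a few table rows. No sample, visit, dose or patient number changes.

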5.2. Secondary Endpoints

The secondary endpoint is the occurrence (yes/no) of adverse events related to the use of local anesthetics, defined as any of the following:

Central nervous system symptoms: seizures, dizziness, loss of consciousness (“attacks”), paresthesia, numbness of the tongue, hyperacusis, tinnitus, visual disturbances, dysarthria, muscle contractions, tremors. Cardiac symptoms: bradycardia, tachycardia, conduction disorder possibly progressing to cardiac arrest. (If at least one of the above events occurs, it will count toward the endpoint.)

6. STUDY DESIGN

6.1. Study Schematic

This is a prospective, descriptive, single-center study. Patients undergoing major abdominal surgery via open laparotomy are included. The epidural catheter is placed at the beginning of the procedure, before induction of general anesthesia. An IV lidocaine bolus of 1.5 mg/kg is given at induction, then continued via infusion pump at 2 mg/kg/h. If the patient is obese (BMI > 30), the dosage will be adjusted based on ideal body weight as a precaution, although there are no specific guidelines on this point. The lidocaine infusion is stopped approximately 30 minutes before the end of surgery. At that same time, the epidural is “activated,” meaning an initial bolus of at least 5 mL of ropivacaine 1 mg/mL is given through the epidural, followed by a continuous infusion starting at a minimum rate of 5 mg/h. This rate will then be adjusted according to the patient’s pain in the recovery room. The total amount of ropivacaine administered will be recorded. Blood samples will be taken for lidocaine level 30 minutes after the bolus, at the end of the infusion, and 2 hours after the start of the epidural ropivacaine infusion. Blood samples for ropivacaine level will be taken 2 hours after the start of the epidural and 24 hours after the start of the epidural. Blood draws will be done through the arterial catheter placed for surgery. In the majority of cases, this catheter is maintained for 24h (patients are admitted postoperatively to a continuous care or intensive care unit). If the arterial line is removed earlier, the 24h ropivacaine sample will be obtained by venous puncture by the ward nurse or investigator. Each blood draw requires 6 mL of blood. The remainder of the anesthetic and analgesic protocol (besides the lidocaine and epidural as described) is left to the discretion of the anesthesiologist in charge of the patient. Patients will be followed for 48 hours postoperatively. Any adverse events related to local anesthetics will be monitored (clinically and with appropriate monitoring such as continuous ECG, etc.).

